### **2.3.4 Participants**

The Federation of Rwandese Football Association (FERWAFA) organizes tournaments at different levels. The top flight male first division is composed of 14 teams while 19 clubs compete in the second division.

The first division competition is the country's primary soccer competition. There are 14 men's association soccer clubs that participate in the league and it operate on the process of promotion and relegation. The teams play 26 matches, where each club plays the others twice, during the season which runs from September to June. The total number of matches is 364 matches. The league is currently sponsored by the largest brewer and soft beverage company in Rwanda on its band new beer named "turbo king" and thus officially known as "turbo king national football league". At the end of the completion, the teams are ranked according to the total points accumulated during the season. In case of equal number of points the goal calculation of the number of goals scored and conceded come in favor of the team to determine the winner. The

league winner qualifies to represent the country in the CAF champions' league while the two lowest placed teams are relegated into the second division. Many teams in the first division are sponsored either by private business companies or government institutions (for example, the police, the army and other governmental parastatals) (FERWAFA, 2008).

There are 19 teams competing in the second division organized by the FERWAFA. Unlike the first division, the second division teams do not play each other because each team would play 36 games. Playing many games require many resources from the teams, the organizing federation as well as a longer period of time. Therefore the teams are randomly divided into two groups. Group A composed of 10 teams and group B composed of 9 teams. Teams in each group play each other and accumulate the points according to the win or draw rules. The first two teams in each group qualify to the semifinal stage where they play the teams from the other group. The winners of the semifinal stage qualify to the final and are automatically promoted to the first division. The competition ends while the teams play between 11 and 12 matches. The second division season runs from November to May. The FERWAFA requires each team to register maximum 30 players; therefore the maximum number of players that will participate in this study are 990.

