Player exposure forms will then be provided to the coaches and will be requested to record every training time that each player participate in soccer activities. Because coaches are focusing on the game during the match, it could be hectic for them to record match exposure. For this reason, match exposure will be obtained from the reports that are submitted by the referee to the FERWAFA.

Before the beginning of each season the FERWAFA set a deadline for the teams to submit the list of all the players that they will use in the league. Therefore the list of all the players will be obtained from the FERWAFA while additional information pertaining to the study will be requested from the team management.

All the medical personnel of the teams will be invited into the briefing meeting that will be held at the FERWAFA premises to explain to them about the study and their task in the study. They will be explained how to fill the injury report forms and they will be asked to report any injury that will take place during data collection. The injury report and exposure forms will be collected by the researcher or the research assistants after every two weeks.

Training and match exposure as well as injury recording for the main study will commence one week before the first game because training performed during that week is for the preparation of the first game. The first division season will start in September 2014 while the second division season will start in November 2014. The exact dates will be obtained from the FERWAFA after the general assembly meeting preparing the league that will take place after the season 2013-2014. Data collection will take place throughout the season up to the last game. Because the FERWAFA allows the teams to recruit new players during the mid season, players who will join the teams halfway through will be recorded from the period recruited. The season will end in June 2015 for the first division and May 2015 for the second division. At the end of the season, the last two teams from the first division are relegated to the second division while the first two teams in the second division are promoted to the first division. A period of rest is given to the

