### **2.3.9 Statistical analysis**

All data will be analyzed statistically using STATISTICA version 12. Standard descriptive statistics will be used for numerical variables as means, standard deviations (SD) or 95% confidence intervals (CI).

In this study incidence for all injuries will be expressed as injuries per 1000 soccer playing hours for the purpose of the comparison with previous epidemiological studies. Risk per 1000 hours of exposure either per match, training or both will be equal to number of injuries multiplied by 1000 per total exposure time. The variations of injuries during match, training or both for the two seasons will be analyzed using Analysis of Variance (ANOVA). ANOVA will also be used to analyze the occurrence of injuries according to the position in the team and division of play. The categorical variables such as the frequency, type, location, severity as well as the mechanism of injuries will be analyzed using a Chi-square test or Fisher's exact test for small numbers. Between groups incidence of injuries will be compared using z-statistics and rate ratios (RR) with a 95% CI will used to present data. The level of significance for all the tests is set to 0.05. Univariate and multivariate regression analyses will be used to calculate odds ratios (ORs) and 95% confidence intervals (CIs) for  $\pm 1$  standard deviation of change. The details of all the statistical analysis that will be performed are provided in the appendix J.

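### Study One's risk-factor regression reports odds ratios with no stated term for hours at risk, and its ANOVA on injury occurrence does not say whether it uses counts or rates

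*Combined protocol and SAP*

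**What the plan says.** Section 2.3.9 uses hours at risk for part of the analysis. Risk per 1000 hours is defined as "number of injuries multiplied by 1000 per total exposure time", and "Between groups incidence of injuries will be compared using z-statistics and rate ratios (RR) with a 95% CI".

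Two other analyses in the same section carry no stated exposure term:

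- **Risk factors:** "Univariate and multivariate regression analyses will be used to calculate odds ratios (ORs) and 95% confidence intervals (CIs", expressed per standard deviation of change. The outcome variable is not defined.
- **Position and division:** "ANOVA will also be used to analyze the occurrence of injuries according to the position in the team and division of play". Occurrence is not defined as a count or a rate.

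The regression serves Study One objective c in section 1.3, on whether intrinsic factors predict injury. Section 2.3.2 does not repeat that objective, but the musculoskeletal tests in section 2.3.5.5 are there to serve it.

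Exposure differs by design. Section 2.3.4 says of the first division: "The teams play 26 matches, where each club plays the others twice, during the season which runs from September to June". Of the second division, whose season runs November to May, it says: "The competition ends while the teams play between 11 and 12 matches". Under section 2.3.6.1, "players who will join the teams halfway through will be recorded from the period recruited". Under the inclusion criteria of section 2.3.4, players who start injured enter only once cleared.

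The hours are collected. Coaches record each player's training time, and match time comes from referees' reports (sections 2.3.5.3 and 2.3.6.1). Section 2.3.9 refers to Appendix J for analysis details.

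**The concern.** An odds ratio for being injured depends on the hourly injury rate and also on how long the player was observed. If the model has no term for hours, any factor that goes with playing time absorbs part of the exposure effect. Fitter players, preferred age groups or certain positions may get more minutes and so look more at risk. A factor that goes with fewer hours can look protective. Previous injury is a plausible example, because players who start injured enter late.

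Objective c is meant to inform prevention, so its results should separate higher risk per hour from more hours. The odds ratios would also be on a different scale from the rate ratios reported beside them.

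The ANOVA wording leaves a related gap. If the outcome is a count, hours are ignored. If it is each player's own rate, an unweighted ANOVA gives a player with few hours the same weight as a regular starter. With a Poisson count at rate λ over T hours, the variance of the observed rate is λ/T, so halving the hours doubles it.

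**Working it through.** **1. The plan's own figures.** Study One states a maximum of 990 players: (14 + 19) teams × 30 = 990, which reproduces. First-division matches per team: 2 × 13 opponents = 26, which also reproduces. No power or event target is given for the Study One regression.

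**2. Exposure ratios, first to second division (section 2.3.4).**

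- Season length: September to June is about 10 months and November to May about 7, so 10/7 = 1.43.
- Matches: 26/12 = 2.17 to 26/11 = 2.36.

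These are proxies. Total exposure includes training, and training hours are not given.

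**3. Odds ratio from exposure alone.** Assume the same constant hourly rate in both groups and an outcome of at least one injury in a season. If the less exposed group has risk p and the other has r times the exposure, then

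- risk in the more exposed group = 1 − (1 − p)^r
- odds ratio = [(1 − p)^(−r) − 1] / [p/(1 − p)]

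Example: p = 0.50 and r = 2.17 give a risk of 1 − 0.50^2.17 = 0.777, odds of 3.49 against 1, and an odds ratio of 3.49. The true rate ratio is 1.

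The only injury proportion in the documents is about 70%, cited in section 2.4.4.3 for Study Two's sample size without a period or division. Risk is therefore varied from 10% to 70% as an assumption.

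| Assumed risk, less exposed group | r = 1.43 | r = 2.17 | r = 2.36 |
|---|---|---|---|
| 10% | 1.46 | 2.31 | 2.55 |
| 30% | 1.55 | 2.72 | 3.09 |
| 50% | 1.69 | 3.49 | 4.15 |
| 70% | 1.96 | 5.39 | 6.95 |

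For a full-season player against one with half the exposure, full-season risks of 30%, 50% and 70% give odds ratios of 2.20, 2.41 and 2.83.

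**4. Simulation.** Group sizes were 14 × 30 = 420 and 19 × 30 = 570, with equal hourly rates, independent players, r = 1.43 or 2.17, second-division risk of 30% or 50%, and 500 runs per scenario. Tests were at the 0.05 level set in section 2.3.9.

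- Logistic regression on injured yes/no: median odds ratio 1.56 to 3.52, rejecting in 91% to 100% of runs.
- ANOVA on injury counts: rejecting in 95% to 100%.
- Poisson regression with log exposure as offset: median rate ratio 0.99 to 1.00, rejecting in 4.4% to 7.2%. The Monte Carlo standard error at 5% is √(0.05 × 0.95/500), about 1 percentage point.

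**5. What this does and does not measure.** The calculation is for two groups that differ in exposure by a known ratio. The planned odds ratios are per standard deviation, which suits continuous measurements such as flexibility or strength. Their bias depends on how strongly each correlates with hours, and the documents give nothing from which to compute it.

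**The case against.** The strongest reply is that the plan already handles exposure where the difference is largest. First against second division is a between-group comparison, and section 2.3.9 compares between-group incidence per hour with rate ratios. That stands. A reader might infer that Study One ignores hours at risk altogether, or that division and joining date will be reported as risk factors with the odds ratios in the table. The documents support neither. Scaling per standard deviation does not fit those two contrasts, and nothing says they will be estimated as odds ratios. Study Two's comparison of incidence between randomised groups (section 2.4.8) follows the Study One incidence method and does not rest on the odds-ratio sentence.

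Three further replies carry weight:

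- Occurrence may mean a rate, since the ANOVA sentences follow the definition of risk per 1000 hours. The ANOVA point is thus an ambiguity and not a shown error.
- Appendix J is not in the text available for this review. It may define the outcome or add exposure as a covariate.
- A factor unrelated to playing time would not acquire a spurious effect by this route.

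These replies do not remove the point. Group-level z-tests and rate ratios cannot supply an adjusted effect per standard deviation of a continuous measurement. For objective c, the only method stated in section 2.3.9 is the one without an exposure term.

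**Conclusion.** The point holds in a limited form. Section 2.3.9 states no exposure adjustment for the risk-factor regression and leaves the ANOVA outcome undefined, in a cohort where hours at risk vary by design. Factors correlated with playing time can then appear to predict injury at equal hourly rates. That they will do so is not shown.

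On size, a contrast carrying a 1.43-fold exposure difference would show a spurious odds ratio of about 1.5 to 2.0, and a 2.17-fold difference about 2.3 to 5.4. This assumes a constant and equal hourly rate, an outcome of at least one injury per season, and season risks of 10% to 70%. The figures show how the mechanism works and do not forecast the bias in any planned estimate. The effect persists at 10% risk, so it does not depend on the 70% figure. The change is worth making before the analysis, mainly for objective c.

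**What to change.** In section 2.3.9, replace the odds-ratio regression with Poisson regression (robust variance) or negative-binomial regression of each player's injury count, with log exposure hours as offset. An equivalent time-to-event model on hours would also serve. Allow for clustering by team and for players observed in both seasons, and report rate ratios with 95% confidence intervals per standard deviation of each factor. Use the same rate model in place of the ANOVA for position and division, so that there is one answer for each contrast on the scale the section already uses for incidence.

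If Appendix J already includes an exposure term, bring section 2.3.9 into line with it, and state the outcome and the adjustment in both places.

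The cost is slightly more modelling and the loss of direct comparability with studies that report odds ratios. No new data are needed, because training and match time are already to be recorded for each player.

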### **2.3.10 Ethical considerations**

Ethical approval to conduct the study will be obtained from the Faculty of Health Sciences Human Research Ethics Committee from the University of Cape Town. Permission to conduct the study will be sought from the Ministry of Sport and Culture and the FERWAFA as well as from the team leaders. The aim of the study will be explained to the coaches and players where they will be provided with the information to empower them to make informed choices about participation in the study. Written informed consent will be obtained from all the participants (Appendices F, G, H, I). The participants will be assured of confidentiality and anonymity. The data will be coded to maintain confidentiality, no names of the participants will be used but they will be assigned a numeric code. Only the researcher would have access to the collected raw data, and it will be kept in a safe locker. Participants will be explained their right to withdraw from the study at any stage without any implication. There is no obvious risk involved in participating in the study. All interested parties will have access to the findings of the study.

## **2.4 STUDY TWO: INJURY PREVENTION INTERVENTION**

### **2.4.1 Aim 1**

One purpose of this study is to explore the difference in the coaches' knowledge, perception of, and readiness to accept a sports injury prevention programme.

#### **2.4.1.1 Objectives**

- a. To assess if there is an increase in the knowledge of coaches towards injury prevention before and after the intervention
- b. To assess if there is any difference in perception of the soccer coaches towards injury prevention before and after intervention
- c. To assess whether the introduction of an injury prevention programme will increase the readiness for injury prevention practice of soccer coaches

### **2.4.2 Aim 2**

A second purpose of the study is to assess the use of a warm up programme on the reduction of injuries in soccer.

#### **2.4.2.1 Objectives**

- a. To assess if there is any difference in the occurrence of injuries before and after the introduction of the injury prevention warm up programme
- b. To assess if the compliance of the injury prevention warm up programme will be associated with the reduction injuries.
- c. To determine if there are any differences in injury incidence and exposure time between groups or over time

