#### **2.4.4.3 Sample size / power analysis**

Based on the study conducted by Twizere (2004), about 70% of soccer players in Rwanda sustained injuries. To obtain a 20% reduction of injuries with the implementation of the 11+ programme with the power of 90% and alpha of 5%, a sample size of 125 in each group (intervention and control) will be required. Taking into consideration the design effect of 2 for cluster randomization, the minimum number of players that should participate in this study is 217.

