#### **2.4.4.4 Recruitment and Sampling method**

As there are 19 teams participating in the second division league, a random sampling method was used to obtain the group with nine or ten teams. Random sampling technique will be done to allocate the teams into the groups. Because of the promotion of the first two teams in the first division and the relegation of the last two teams into the second division, the teams will be selected towards the beginning of the season 2014-2015.

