Coaches will also be trained on first aid. During the training, they will receive the first aid course for two days that will be provided by the trainer from the Rwanda Red Cross. Questionnaires will be distributed to the coaches to assess their knowledge immediately after first aid training. At the end of season two (June 2016) questionnaires will be distributed to the coaches from both divisions to assess the knowledge retained after one year of intervention.

Coaches and medical personnel from the first division will be requested to continue the recording of injuries and exposure using the procedure they used in the season one (2014-2015). To increase compliance and proper recording, coaches will be visited at team practice by the researcher to see if proper implementation is occurring and additional instructions on the correct conduct of the exercises will be provided where necessary. Data collection during season two (2015-2016) will be the same as season one where players exposure time, occurrence of injuries, treatment will be assessed.

Figure 3: Study two framework

[figure not shown]

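### Each team's 2014-15 injury rate could serve as a covariate in the randomised comparison at no data cost; the available text leaves the comparison unadjusted and tests the programme partly by an uncontrolled before-after objective

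*Combined protocol and SAP*

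**What the plan says.** - **Objectives (2.4.2.1).** Objective (a) is "To assess if there is any difference in the occurrence of injuries before and after the introduction of the injury prevention warm up programme". No comparator is named. Objective (c) concerns incidence and exposure between groups or over time.
- **Data (2.3.6.1 and 2.4.7.1).** Both divisions record injuries and exposure through 2014-15. For the intervention season, "Data collection during season two (2015-2016) will be the same as season one".
- **Allocation (2.4.4.4).** "Random sampling technique will be done to allocate the teams into the groups". No stratification, matching or constraint is mentioned. The same section places the selection of teams near the start of 2014-15, whereas 2.3.6.1 starts the intervention study with the 2015-16 season.
- **Analysis (2.4.8, referring to 2.3.9).** Incidence in the two arms is compared by z-statistics and rate ratios with 95% intervals. The two seasons are compared by ANOVA. Neither analysis is given a baseline covariate, a team term or an arm-by-season term. Both sections leave the full detail to Appendix J, which is not in the available text.

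**The concern.** A before-after change takes in everything that differs between the two seasons. The protocol itself expects new players, coaches, teams and medical staff, as well as promotion and relegation (2.3.6.1, 2.4.7.1). The injury form is not in routine use in Rwanda (2.3.5.4), so recording may also shift as recorders learn it. A fall or a rise in injuries under objective (a) could not be credited to the 11+, although randomised controls are followed over the same season.

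With only 19 teams, differences between teams make up a large part of the error in the arm comparison. A team's rate in the previous season, recorded in the same way, is the most obvious predictor of its next rate. Leaving it out gives up precision that needs no new data.

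**Working it through.** **Inputs.** From 2.4.4.3: "about 70% of soccer players in Rwanda sustained injuries" and "the design effect of 2 for cluster randomization". From 2.4.4.4: 19 teams, split 9 and 10. From 2.3.4: at most 30 players per team, taken here as 30. The documents give no season-to-season correlation r, so a range is assumed.

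**Plan's own figure.** For 70% against 50%, two-sided 5%, 90% power, pooled variance:
n = [1.96·√(2·0.6·0.4) + 1.2816·√(0.7·0.3 + 0.5·0.5)]² / 0.2² = (1.358 + 0.869)² / 0.04 ≈ 124 per group. The stated 125 is reproduced, which supports 70% as the base rate. The stated total of 217 does not follow (125 × 2 groups × 2 = 500); that is a separate matter and is not used below.

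**Team-to-team variation implied by the plan.**
- ICC = (2 − 1)/(30 − 1) = 0.034.
- Team proportion: SD = √(0.21 × 2/30) = 0.118; CV = 0.118/0.70 = 17%.
- Counts (Poisson-type assumption): 70% injured implies −ln(0.30) = 1.204 injuries per player, or 36.1 per team; CV = √(2/36.1) = 24%.

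**Chance imbalance.** The SD of the arm difference, in team SDs, is √(1/9 + 1/10) = 0.459. P(arms differ by more than 20%) = 2[1 − Φ(0.20/(CV × 0.459))].

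| Team CV | P(difference > 20%) |
|---|---|
| 17% | 1% |
| 24% | 6% |
| 30% (assumed) | 15% |
| 40% (assumed) | 28% |
| 50% (assumed) | 38% |

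A CV of 30% would need a design effect of about 0.30² × 36.1 = 3.3 (counts) or 0.30² × 0.70² × 30/0.21 = 6.3 (proportions), against the plan's 2.

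Smaller imbalances are common. The SD of the observed difference in proportion injured is √[0.21 × 2 × (1/270 + 1/300)] = 5.4 points, so a gap above 5 points has a chance of about 36%. The plan's target is 14 points (70% to 56%, a relative reading of 20%) or 20 points (70% to 50%).

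**Plausible r.** The reliability of one season's team rate is 30 × 0.0345/2 = 0.517. If the stability of the true team effect is 0.5 to 1.0 (assumed), r = 0.26 to 0.52.

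**Gain from adjustment.** Variance multipliers relative to the unadjusted comparison:

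| r | Covariate, 1 − r² | SE factor | Change score, 2(1 − r) |
|---|---|---|---|
| 0.26 | 0.93 | 0.97 | 1.48 |
| 0.52 | 0.73 | 0.85 | 0.96 |

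The change score is worse than no adjustment whenever 2(1 − r) > 1, that is, r < 0.5. It is never better than the covariate, since 2(1 − r) − (1 − r²) = (1 − r)².

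**Small-sample cost.** Estimating one slope from 19 teams inflates the variance by about 1 + 1/(17 − 2) = 1.067 (normal covariate). The SE factors become √(0.932 × 1.067) = 1.00 at r = 0.26 and √(0.730 × 1.067) = 0.88 at r = 0.52. Break-even is 1 − r² = 15/16, or r = 0.25.

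**The case against.** Simple randomisation is unbiased, and a standard error that respects teams already allows for chance imbalance. Adjustment is therefore a gain in efficiency, not the repair of a bias. That stands, with the proviso that the z-statistic in 2.3.9 names no team-level error.

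Four stronger readings are tempting, and the documents do not support them:

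- **Season-one data serve only the before-after objective.** They also serve Study One. Objective (c) and the two-season ANOVA could draw on them, and first-division teams continue recording as a non-randomised concurrent series. What is missing is a specified baseline-adjusted contrast. The multivariate regression in 2.3.9 yields odds ratios per standard deviation and is not tied to the arm comparison.
- **Every team has a usable baseline.** Section 2.4.7.1 allows for newly registered teams. Relegated teams bring rates from a league of 26 matches instead of 11 to 12, and the recorder may differ, because research assistants record where there are no medical staff (2.3.5.4).
- **Season-one rates should have been used to balance the arms.** On the date in 2.4.4.4 they would not yet exist. The reason given there (promotion and relegation) and the 2015-16 start suggest a later date, but the text does not settle it.
- **The arms coincide with the league groups.** Section 2.3.4 describes "Group A composed of 10 teams and group B composed of 9 teams", and the split of teams has the same sizes. No section says that the two are the same.

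**Conclusion.** The point holds as a free improvement. The available text plans a pre-intervention rate for most teams, leaves it out of the randomised comparison, and lists an uncontrolled before-after objective that cannot isolate the programme. Confidence is limited because Appendix J may specify an adjustment.

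The gain in precision is modest. The SE factor is 0.97 to 0.85 for an assumed r of 0.26 to 0.52, or about 1.00 to 0.88 after the small-sample cost, so below about r = 0.25 nothing is gained. It would be larger if players' own injury-proneness carries over between seasons and raises r.

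A reader might infer that a large baseline imbalance is likely. The plan's design effect does not bear that out: the chance of a difference above 20% is about 1% to 6%, and it reaches 15% only at a team CV of 30%. These figures rest on 30 players per team (a maximum), a design effect of 2 and normal approximations. The firmer benefit is a controlled answer to the question behind objective (a).

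**What to change.** 1. **Analysis.** Make the between-arm comparison of 2015-16 team injury rates the test of the programme, in a team-level or cluster-adjusted model with each team's 2014-15 log injury rate as a covariate. Do not use a change score or an unconstrained arm-by-season term. State a convention for a team with no recorded injuries.
2. **Missing baselines.** Give a team without a season-one record the mean value plus an indicator. If only one team is affected, use the mean value alone, because in a team-level model the indicator would remove that team from the contrast. Note which teams bring first-division rates.
3. **Objective (a).** Relabel it as descriptive and report before-after figures by arm.
4. **Allocation.** Reconcile the selection date in 2.4.4.4 with the 2015-16 start in 2.3.6.1. Only if allocation follows season one, consider constrained randomisation on the season-one rate. Full stratification on several factors is impractical with 19 teams.
5. **Text.** If Appendix J already contains such an adjustment, state it in 2.4.8.

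Cost: one covariate (1 of 17 degrees of freedom, and a second if the indicator is used), a per-team summary of season one, and no new data.
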